## Abstract

**Background:**

Preventive home visits to elderly people by public health nurses aim to maintain or improve the functional status of elderly and reduce the use of institutional care services. A number of trials that investigated the effects of home visits show positive results, but others do not. The outcomes can depend on differences in characteristics of the intervention programme, but also on the selection of the target population. A risk group approach seems promising, but further evidence is needed. We decided to carry out a study to investigate the effects in a population of elderly with (perceived) poor health rather than the general population. Also, we test whether nurses who are qualified at a lower professional level (home nurses instead of public health nurses) are able to obtain convincing effects. The results of this study will contribute to the discussion on effective public health strategies for the aged.

**Methods/design:**

The study is carried out as a parallel group randomised trial. To screen eligible participants, we sent a postal questionnaire to 4901 elderly people (70–84 years) living at home in a town in the south of the Netherlands. After applying inclusion criteria (e.g., self-reported poor health status) and exclusion criteria (e.g., those who already receive home nursing care), we selected 330 participants. They entered the randomisation procedure; 160 were allocated to the intervention group and 170 to the control group. The intervention consists of (at least) 8 systematic home visits over an 18 months period. Experienced home nurses from the local home care organisation carry out the visits. The control group receives usual care. Effects on health status are measured by means of postal questionnaires after 12 months, 18 months (the end of the intervention period) and after 24 months (the end of 6-months follow-up), and face-to-face interviews after 18 months. Data on mortality and service use are continuously registered during 24 months. A cost-benefit analysis is included.

The design and setting of the study, the selection of eligible participants and the study interventions are described in this article. Other included items are: the primary and secondary outcome measures, the statistical analysis and the economic evaluation.

## Background

The number of elderly people is increasing. Due to the ageing population, more demands are made on health care services [1]. In the last two decades, preventive programmes have been developed aiming at reducing health care cost and improving the independent functioning of elderly people. One of such programmes is home visitation by public health nurses of elderly people living in the community. This aims to maintain or improve the functional abilities and well-being of elderly people and reduce the use of institutional care services. Such programmes for elderly people are part of national policy in several countries, including the UK, Denmark and Australia. However, the results of trials on the effects of home visits have been inconsistent [2]. Investigators are still in search of the most effective strategy.

In the past years 3 reviews were published on the effects of preventive home visits to elderly people living in the community [2-4]. These used different methodological approaches. Apart from a number of similar trials, each review also included a series of different trials, depending on the inclusion criteria and the date of publication. Van Haastregt *et al *[2] reviewed 15 studies and concluded that no clear evidence exists for the effectiveness of the visits: the observed effects are considered to be fairly modest and inconsistent. Nine trials reported at least one (significant) favourable effect and 6 trials reported no effects. In most of the studies the intervention was aimed at the general population aged 65 years or over, without any selection. The other 2 reviews [3,4] included a meta-analysis of the data and were more positive about the effects of the home visits. Stuck *et al *[4] indicated that home visits can reduce the risk of functional decline and nursing home admission, provided that the interventions are based on a multi-dimensional geriatric assessment and include multiple follow-up visits. Home visiting programmes improved functional status more in people with the lowest mortality risk (younger population, < 80 years). Elkan *et al *[3] reported a favourable effect on mortality and nursing home admissions among members of the general population and frail older people who are at risk of adverse outcomes. However, they did not find improvement in functional status.

One can argue about the differences in the approach of each review, but in general the results of the home visiting studies are heterogeneous with respect to the different outcome measures. Many factors can play a role in the effectiveness of the interventions, including the target population, characteristics of the intervention, the persons carrying out the visits and the compliance to the given advice.

Research in the Netherlands showed that preventive home visits do not seem to be useful for the general population of elderly people [5]. In that trial, experienced public health nurses visited the intervention group (n = 300) at least four times a year over a period of 3 years. The control group (n = 300) received usual care. After 3 years, no or hardly any effects were demonstrated on the health and service use of the total group of visited elderly (see table 1). However, a subgroup analysis indicated that the visits seemed to be effective for elderly with a poor (perceived) health status. Visited persons with poor health at baseline scored considerably better on several health measures (e.g., functional status) compared to similar persons in the control group. Mortality rates after three years were lower (24% versus 40%) and substantial effects were found for referrals to outpatient clinics (61% versus 79%) and also for hospital admissions, especially re-admissions. In the intervention subgroup 47% were admitted at least once to the hospital, with a total of 1,134 days; in the control subgroup these figures were 74% and 2,043 days (table 1). These effects emerged already during the first year of the intervention period [6].

The probable usefulness of home visits for a high risk group was confirmed in five controlled studies [7-11]. However, the results of three other trials did not support this assumption [12-14]. Although home visits for a restricted population seem a promising approach, further evidence is needed. The findings of the earlier Dutch subgroup analysis were based on a relatively small number of subjects (53 in the control and 57 persons in the intervention group). Therefore, we decided to carry out a new trial in which the risk group approach is tested in a larger population of those with (perceived) poor health. At the same time, we appointed nurses who are qualified at a lower professional level (enrolled home nurses instead of public health nurses) to carry out the visits. An experienced public health nurse will supervise them.

This study will investigate the effects of systematic home visits by home nurses to elderly people with (perceived) health problems in terms of their health status, the use of care services and the cost-effectiveness. We expect that the visits will improve the functional abilities, perceived health and quality of life of the participants. We also hypothesize that they will reduce specialist care, institutionalisation, especially hospital (re-) admissions, and total health care expenditures. Evidence regarding the usefulness of the proposed risk group approach is needed to decide on the future implementation of the visits. This article presents the design of this new trial.

## Methods/design

### Study design and setting

The study is carried out as a parallel group randomised trial. It is conducted in co-operation with a large home care organisation in the south of the Netherlands (Sittard and surroundings). The addresses we used to screen eligible persons for the study were drawn from the population register of the municipality. After the screening procedure we randomised 330 elderly. Effects of the intervention are measured by means of postal questionnaires after 12 months, 18 months (at the end of the intervention period) and after 24 months (at the end of a 6-months follow-up period) and by face-to-face interviews after 18 months. Mortality and data on the use of care services are continuously registered over the 24-months research period. A cost-benefit analysis is also included. The design of the study is shown in figure 1. The design is, unless otherwise mentioned, carried out according to plan.

The study has obtained the approval by the Medical Ethical Committee of Maastricht University/Academic Hospital Maastricht.

### Identification of eligible participants

We sent a postal questionnaire to 4901 elderly people between the age of 70 and 84 years who were still living at home. These lived in 14 districts in the research area. We included districts with close proximity to the centre of town where the home care organisation is situated. In this way we limited the travelling time of the nurses to carry out the visits. Districts with large industrial areas were excluded.

Reminders were sent after 2–3 weeks to 45% of the elderly. The response rate was 76% after about 6 weeks. The response rates per district fluctuated between 65% and 81%. The average time to fill out the questionnaire was about 30 minutes. The elderly could do this by themselves or, if they needed help, with the assistance of family, friends or volunteers. A list of names and addresses of volunteers was added to the questionnaire. Even if persons did not want to participate in the study, we kindly requested them to fill out the questionnaire and return it to us. A postage free envelope was included.

The questionnaire was used as a screening instrument and also served as a baseline measurement for the participants of the trial. Among the respondents (n = 3,689, see figure 1), we found 872 persons who reported their health status as poor (on a scale ranging from 1–10 points, report marks 1–5 are considered poor, 6–7 fairly good, and 8–10 good). Our previous home visitation study indicated positive effects for this subgroup. Five persons did not sign the informed consent form and 273 persons with a poor health status did not want to participate in the study. Of the remaining 594 persons, we excluded those who already received home nursing care at baseline, in order to avoid contamination of (other) nursing care. Referral to nursing services after the start of the intervention period has no consequences for the scheduled home visits in the intervention group. It is regarded as a possible effect of the intervention and it is registered as outcome in terms of service use. Persons on a waiting list for admission to nursing homes or homes for the elderly were also excluded. The local independent committee dealing with applications for the use of care services already granted them this service. It is likely that most of them already receive regular supervision of professional caregivers. Six persons were excluded on the advice of their GPs. They were severely or terminally ill and would probably die within 6 months. On the basis of these exclusion criteria, a total of 102 persons were excluded.

After applying the in- and exclusion criteria, 492 persons were eligible to take part in the study. However, we excluded 162 more persons for the following reasons: their GP did not want to co-operate with the study (n = 139), respondents had too many missing values on the functional status scale (n = 11), the health insurance company was unknown (n = 1) or it was uncertain whether the health insurance company would be willing to co-operate (n = 11). The health insurance companies of 96% of the finally selected participants had already given consent to provide us with data on health service use. As we selected persons whose GP was willing to co-operate, relevant health care data from the GP practices are available for all participants. A flow diagram of the selection of participants is shown in figure 1. Finally, 330 persons entered the randomisation procedure. In consideration of the available working hours of the nurses, the maximum number of participants to receive home visits was 160. The control group was hence set at 170.

#### Sample size consideration

We calculated the sample size from the data of our previous home visitation study in the Netherlands [5]. Participants were categorized on the primary outcome measure self-rated health, perceiving their health status as (a) better or the same compared to the start of the study, or (b) worse or deceased. We expect to demonstrate a difference of 20% between the study groups (65% score (a) in group I versus 45% in group II). Based on a 0.9 power to detect a significant difference (α = 0.05, one-sided), 104 participants are required for both study groups. Accounting for a loss to follow up of 30%, we planned to enrol 150 participants per group. This number is also large enough (again extrapolated from our own data) to detect differences in specialist care and institutionalisation (e.g., to detect a difference in mean hospital days of 10 days over a 1.5 year period).

Based on data of the selection criteria we estimated that about 10% of the screened population was eligible for the study (including informed consent). Therefore, we needed to mail a minimum of 3,500 questionnaires to persons aged 70–84 years living in the community. To account for unforeseen circumstances, we decided to send out about 5,000 questionnaires. After applying the inclusion and exclusion criteria, and taking into account the GPs' willingness to co-operate with the study, there were sufficient participants eligible for the study to raise the selected number to 330. This slightly increased the power of the study.

#### Randomisation

The baseline measurements included questions on relevant prognostic factors related to the health status and service use. Before randomisation we divided the 330 participants into two groups: couples (n = 46) and those for whom this did not apply (n = 284). In this way we made sure that eligible persons who lived together, were always allocated to the same study group (in order to avoid contamination of the intervention). The 23 couples were divided into 3 strata on the basis of their (added) score on functional status (0–4, 5–7 or more than 7 out of 18 activities that cannot be carried out independently). The other 284 participants were stratified into 8 strata based on 3 prognostic factors – two health-variables and one service use-variable:

1. functional status (0–2 or more than 2 activities that the elderly cannot carry out independently)

2. changes in health during the 3 months prior to completion of the questionnaire (same/better or worse)

3. contact with a medical specialist in the 3 months prior to completion of the questionnaire (contact yes or no).

The participants in each of the 8 strata were then randomised into either a control or intervention group using a computer generated randomisation list with a block length of 4 [15]. Randomly, we allocated 160 persons to the intervention group and 170 persons to the control group. Table 2 shows the baseline characteristics of the intervention and control group. The study groups are well matched; there were hardly any differences between the groups at the start of the study.

The participants in the intervention group were assigned to one of the three home nurses. This depended on the location of their GP practice, as each nurse was assigned to a number of GP practices. We assumed that this would facilitate the co-operation with the GPs. Each nurse was responsible for 52–56 elderly during the intervention period.

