### Statistical analyses

The main analyses will be conducted according to the intention-to-treat principle. Analysis of primary and secondary endpoints will be performed using relevant significance tests (e.g., chi-square, t-test or analysis of variance). Regression techniques will be used, if necessary, to estimate the effects for the various outcome measures, adjusting for small differences between the groups at the start of the study. In addition, we will conduct per-protocol analyses; these are restricted to those participants who complied fully with the intervention protocol and outcome measurements. Preplanned subgroup analysis will be performed for the following subgroups: living alone/together; health deterioration over the previous 3 months; functional status and locus of control. Differences in approaches between the nurses will be investigated.

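### Couples were allocated as units, but the named tests assume independent individuals, so standard errors are slightly too small for outcomes that correlate positively within couples

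*Protocol article*

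**What the plan says.** The Randomisation section of the protocol article divides the 330 participants into "couples (n = 46) and those for whom this did not apply (n = 284"). The purpose was to prevent contamination between partners: "In this way we made sure that eligible persons who lived together, were always allocated to the same study group". Couples had their own stratification: "The 23 couples were divided into 3 strata on the basis of their (added) score on functional status". The others were placed in 8 strata formed from functional status, recent change in health and recent specialist contact. The result was: "Randomly, we allocated 160 persons to the intervention group and 170 persons to the control group".

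The Statistical analyses section then says: "Analysis of primary and secondary endpoints will be performed using relevant significance tests (e.g., chi-square, t-test or analysis of variance"). Regression is conditional and has a stated purpose: "Regression techniques will be used, if necessary, to estimate the effects for the various outcome measures, adjusting for small differences between the groups". People living alone and people living together form one of the preplanned subgroup comparisons.

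The sample size section counts individual participants: "Based on a 0.9 power to detect a significant difference (α = 0.05, one-sided), 104 participants are required for both study groups". None of these sections mentions correlation within couples, the household as a unit of analysis, or a variance estimator that allows for clustering.

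**The concern.** Allocating two people together makes the couple the unit of randomisation for those two people. If partners' outcomes are positively correlated, a couple carries less information than two unrelated participants. A test that counts them as two independent observations then gives a standard error that is too small.

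The article gives reason to expect some positive correlation. Partners were kept together because contamination between them was feared. Several service-use outcomes are also partly properties of the household, such as domestic care and modifications to the home.

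At stake are slightly narrow confidence intervals and a type I error slightly above nominal. This matters most when a result lies close to the one-sided 5% limit used in the sample size calculation. The subgroup of people living together needs separate thought because all 46 members of couples fall into it.

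**Working it through.** **Inputs.** From Randomisation: 330 people, 23 couples (46 people), 284 others, 160 intervention and 170 control. From Sample size consideration: 65% versus 45%, one-sided alpha 0.05, power 0.90, 30% loss. The within-couple ICC is not given, so it is an assumption shown over a range.

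**Units randomised.** 284 + 23 = 307. Share of participants in couples: 46/330 = 13.9%.

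**The plan's own figure.** For two independent proportions with pooled variance and no continuity correction:

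n = [1.645·√(2·0.55·0.45) + 1.282·√(0.65·0.35 + 0.45·0.55)]² / 0.20² = (1.157 + 0.883)² / 0.04 ≈ 104.1

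This rounds up to 105, against the stated 104. Then 105/0.7 = 150 per group, as planned. The stated number is thus reproduced by a formula for independent individuals with no design effect.

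**Design effect.** For clusters of size 1 and 2:

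DEFF = 1 + ICC·Σm(m−1)/N = 1 + ICC·(23·2·1)/330 = 1 + 0.139·ICC

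The naive standard error is too small by 1 − 1/√DEFF. The one-sided type I error of the naive test is 1 − Φ(1.645/√DEFF). Required n is 104·DEFF. Power is for 160 and 170 enrolled with 30% loss (112 and 119 analysed), each divided by DEFF.

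| Assumed ICC | DEFF | Naive SE too small by | One-sided type I error | Effective N of 330 | Required n per group | Power |
|---|---|---|---|---|---|---|
| 0 | 1.000 | 0% | 0.050 | 330 | 104 | 92.5% |
| 0.1 | 1.014 | 0.7% | 0.051 | 325 | 106 | 92.2% |
| 0.3 | 1.042 | 2.0% | 0.0535 | 317 | 109 | 91.5% |
| 0.5 | 1.070 | 3.3% | 0.056 | 308 | 112 | 90.9% |
| 1 (limit) | 1.139 | 6.3% | 0.062 | 290 | 119 | 89.3% |

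**Split of couples between arms.** The article does not say how the couples divided. At ICC 1 the ratio of correct to naive standard error is 1.064 with all couples in control and 1.071 with all in intervention, against 1.067 in the table. The split hardly matters.

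**Subgroup living together.** Its size is not in the text. Assume for illustration that it holds 165 to 198 people (50 to 60% of 330). The share in couples is then 46/198 = 0.232 to 46/165 = 0.279. DEFF is 1.07 to 1.08 at ICC 0.3 and 1.12 to 1.14 at ICC 0.5, with one-sided type I error of about 0.056 to 0.062. A smaller subgroup would raise these figures and a larger one would lower them.

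**The case against.** The strongest reply is that the tests are listed only as examples, in a condensed article, and that regression is allowed. Handling of paired participants could well be settled in a fuller document. This stands in part. A reader might infer that the plan states all 330 people will be treated as independent, but the article does not say so. What remains is that every named test shares the independence assumption, and that regression is given a different purpose. The methods the article does name therefore do not match the allocation it describes.

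A second reply is that the direction of the error is not certain. This also stands. A reader might infer that type I error is inflated for every outcome, but that needs a positive within-couple correlation on every outcome, and the article gives none. Unadjusted tests also ignore the stratification on prognostic factors, which tends to make standard errors too large. As an illustration, at ICC 0.3 the couple effect adds 4.2% to the variance, and strata explaining about 4% of outcome variance would roughly cancel it. That offset is unquantified and would disappear once regression adjusts for those factors, so it is no basis for leaving the couples out of account.

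A third reply is that the effect is small. It is: 284 of the 330 people were allocated individually.

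Two further inferences should be resisted. The article does not say that partners share the nurse's visits; it describes an individual plan for each person, and control couples receive no visits. Nor is there a wrong cost test to correct, because the economic evaluation section names no inferential method.

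**Conclusion.** The point holds as a minor mismatch between allocation and analysis. For outcomes that correlate positively within couples, the named tests understate standard errors by about 1 to 3% at an assumed ICC of 0.1 to 0.5, and a one-sided 5% test runs at about 5.1 to 5.6%. With couples spread proportionally over the arms, the limit at ICC 1 is 6.3% and 6.2% respectively. These figures rest on the assumed ICC and leave aside any opposing effect of ignored stratification.

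The relative effect is larger among people living together, but it cannot be fixed from the text because the subgroup's size is not given.

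It might be inferred that the trial is too small because 307 units were randomised rather than 330. The figures do not support that. At ICC 0.5 the required number is 112 per group, and 112 and 119 remain after 30% loss. Power falls just below 90%, to 89.3%, only at the limiting ICC of 1. The sample size and the main conclusion are not threatened.

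**What to change.** State that individual-level outcomes, including the comparison of people living alone and together, will be analysed with household-clustered robust standard errors or with GEE, treating people outside couples as clusters of size one. Include the randomisation strata (8 for those outside couples, 3 for couples) as covariates, so that ignoring the stratification does not distort the standard errors in the other direction. With only 23 pairs the within-couple correlation will be estimated imprecisely, so inference should rest on the robust variance.

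If confidence intervals for costs are bootstrapped, resample households rather than persons.

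The cost is minimal. Couple membership is already recorded from randomisation, no further data are needed, and the clustering itself makes intervals only slightly wider. The choice should be recorded before outcome data are analysed by arm.
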